### **8.1.2. Safety Lead-In Definition of Dose Limiting Toxicity**

DLT is defined as one or more of the following:

- Total of  $\geq 7$  days of lenalidomide and/or  $\geq 1$  dose of cetuximab missed during the first cycle due to drug-related toxicity as outlined below:
  - Any Grade 3 or 4 non-hematological toxicity (excluding alopecia), even after optimally treated with supportive measures.
    - A rash with suspected relationship to cetuximab, treated and resolved in accordance with the guidelines will not be considered a DLT.
  - Grade 4 neutropenia or febrile neutropenia.
  - Grade 4 thrombocytopenia.

Should any subject discontinue the study prior to completing the entire first cycle for reasons other than a DLT or if  $\geq 7$  days of lenalidomide and/or  $\geq 1$  dose of cetuximab were missed during the first cycle for reasons other than a DLT, then a replacement subject will be added at that dose level.

The occurrence of one of the above drug-related toxicities will result in a clinical and/or laboratory assessment to be performed within 7 days following the initial finding to examine the subject for resolution of the toxicity. Lack of resolution of any of these toxicities according to the guidelines above or within 7 days of scheduled start of Cycle 2 Day 1 will be considered a DLT. Subjects who experience a DLT may continue on treatment at the Investigator's discretion at a lower dose of lenalidomide in accordance with [Table 6](#).

Adverse events will be graded using the CTCAE Version 4.0 ([http://ctep.cancer.gov/protocolDevelopment/electronic\\_applications/docs/ctcae4.pdf](http://ctep.cancer.gov/protocolDevelopment/electronic_applications/docs/ctcae4.pdf)).

If cetuximab is discontinued, lenalidomide may be continued until documented tumor progression, unacceptable toxicity, death, or treatment discontinuation for any other reason.

Following Cycle 1, all subjects will continue on assigned treatment until documented tumor progression, unacceptable toxicity, death, or treatment discontinuation for any other reason and be followed for toxicity and secondary endpoints.

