### **10.3. Dose Modification or Interruption**

Dose modifications of lenalidomide and cetuximab are not permitted during Cycle 1 of the Phase 2a – Safety Lead-In part, unless a subject experiences a DLT, however permitted anytime after Cycle 1 during Phase 2a – Safety Lead-In, anytime during Phase 2b –POC and Phase 2b – Expansion.

For toxicities consistent with cetuximab administration, discontinuation, dose interruptions and/or reductions see Section 10.3.2 and the approved product labeling. If toxicities are believed to be attributed to lenalidomide administration, please see Table 6 for dose modification guidelines. Doses of any investigational product cannot be re-escalated once reduced. Any investigational product (lenalidomide and/or cetuximab) held > 14 days must be discontinued. If cetuximab is discontinued per protocol and for reasons other than disease progression, lenalidomide may be continued until documented tumor progression, unacceptable toxicity, death, or treatment discontinuation for any other reason.

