### 10.3.1. Lenalidomide Dose Modification or Interruption

**Table 6: Dose Modification Guidelines for Lenalidomide**

| Toxicity                                                            | Grade | Dose Modification                                                                                                                                                                                                                                                                                    |
|---------------------------------------------------------------------|-------|------------------------------------------------------------------------------------------------------------------------------------------------------------------------------------------------------------------------------------------------------------------------------------------------------|
| Rash                                                                | 3     | Hold lenalidomide until resolution to $\leq$ Grade 2; at first occurrence resume at same dose of lenalidomide; at second occurrence resume lenalidomide at 5 mg reduction in dose. Further dose reductions are permitted to a minimum of 5 mg.
If rash is desquamating, discontinue lenalidomide. |
|                                                                     | 4     | Discontinue lenalidomide.                                                                                                                                                                                                                                                                            |
| Sinus bradycardia, atrial fibrillation or other cardiac arrhythmias | 2     | Hold lenalidomide until resolution to $\leq$ Grade 1, resume lenalidomide at 5 mg reduction in dose. Additional dose reductions are permitted to a minimum of 5 mg.                                                                                                                                  |
|                                                                     | 3 / 4 | Discontinue lenalidomide.                                                                                                                                                                                                                                                                            |

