| Neutropenia                                                         | 3 / 4 | Hold lenalidomide, CBC weekly until resolution to $\leq$ Grade 2, resume lenalidomide at 5 mg reduction in dose. Additional dose reductions are permitted to a minimum of 5 mg.                                                                                                                      |
| Thrombocytopenia                                                    | 3 / 4 | Hold lenalidomide, CBC weekly until resolution to $\leq$ Grade 2, resume lenalidomide at 5 mg reduction in dose. Additional dose reductions are permitted to a minimum of 5 mg.                                                                                                                      |
| Venous thrombosis or embolism                                       | 3     | Continue lenalidomide and anticoagulate.                                                                                                                                                                                                                                                             |
|                                                                     | 4     | Discontinue lenalidomide and anticoagulate.                                                                                                                                                                                                                                                          |
| Allergic reaction or hypersensitivity                               | 2 / 3 | Hold lenalidomide until resolution to $\leq$ Grade 1; resume lenalidomide at 5 mg reduction in dose. Additional dose reductions are permitted to a minimum of 5 mg.                                                                                                                                  |
|                                                                     | 4     | Discontinue lenalidomide.                                                                                                                                                                                                                                                                            |

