### **10.6. Discontinuation from Treatment**

The following events are considered sufficient reasons for discontinuing a subject from investigational product(s):

- Adverse event(s) (AEs) that, in the judgment of the Investigator, may cause severe or permanent harm or which rule out continuation of investigational product(s).
- Disease progression
- Subject withdraws consent
- Subject lost to follow-up
- Death
- Protocol violation

The reason for discontinuation should be recorded in the CRF and in the subject's medical records. An IVRS call is required when discontinuing any investigational product.

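### Lead-in Cycle 1: Section 10.3 bars a dose reduction that Table 6 orders, and subjects who lose 7 or more lenalidomide days to an unlisted drug-related toxicity are replaced instead of counted towards the MTD

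*Protocol*

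**What the plan says.** Three parts of the protocol govern a subject with a low blood count in lead-in Cycle 1.

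- **Section 8.1.2 (and the synopsis).** The main DLT route is 7 or more lenalidomide days, or at least one cetuximab dose, "missed during the first cycle due to drug-related toxicity as outlined below". For blood counts the list is "Grade 4 neutropenia or febrile neutropenia" and Grade 4 thrombocytopenia. It also covers Grade 3 or 4 non-hematological toxicity, apart from alopecia and treated, resolved cetuximab rash. A second route is failure of these same toxicities to resolve. A subject who leaves the study in Cycle 1 for a reason other than a DLT is replaced. So is one for whom that much lenalidomide or cetuximab dosing was missed; the text says these doses "were missed during the first cycle for reasons other than a DLT, then a replacement subject will be added at that dose level".
- **Section 10.3.** Dose modifications of either drug "are not permitted during Cycle 1 of the Phase 2a – Safety Lead-In part, unless a subject experiences a DLT". Also: "Any investigational product (lenalidomide and/or cetuximab) held > 14 days must be discontinued".
- **Table 6**, titled "Dose Modification Guidelines for Lenalidomide". For Grade 3 or 4 neutropenia, and likewise thrombocytopenia, the instruction is "Hold lenalidomide, CBC weekly until resolution to" Grade 2 or lower, then resume 5 mg lower. Lead-in Cycle 1 is not excepted.

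Section 8.1.3 defines the MTD as the highest dose with no more than 1 DLT in 6 subjects during Cycle 1.

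**The concern.** There are two separate problems.

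The first is a conflict of instructions. A site that sees a drug-related Grade 3 neutropenia in lead-in Cycle 1 is told by Table 6 to hold lenalidomide and resume at a lower dose, and by Section 10.3 not to modify the dose because no DLT has occurred.

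The second concerns the count. A subject whose lenalidomide is stopped for 7 days or more by a drug-related toxicity that Section 8.1.2 does not list has not had a DLT. The replacement clause then removes that subject from the six. A toxicity serious enough to interrupt the test dose for a quarter of the cycle leaves no trace in the decision rule.

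The MTD is the Phase 2a primary endpoint. It sets the combination dose for up to 41 proof-of-concept subjects and, if the study proceeds with the combination, about 120 expansion subjects. The lead-in gives lenalidomide on all 28 days with cetuximab, whereas the solid-tumor study cited in Section 5.2.5 gave it alone on Days 1-21. Tolerability of this schedule therefore has to be learned here.

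**Working it through.** **Step 1: can 10.3 and Table 6 both be followed?** Take a non-febrile, drug-related Grade 3 neutropenia in Cycle 1, with a hold of under 7 days and no cetuximab dose missed.
- It is not a missed-dose DLT: Grade 3 is not listed and fewer than 7 days are missed.
- It is not a non-resolution DLT: that route covers only the listed toxicities.
- Table 6 requires resumption 5 mg lower; Section 10.3 forbids it. This holds even if the bar in 10.3 covers reductions only and leaves holds free.

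**Step 2: who is replaced?** The subject must miss 7 or more lenalidomide days (or a cetuximab dose), or leave the study in Cycle 1, for a non-DLT reason. A hold of 1 to 6 days leaves the subject evaluable as a non-DLT. Cycle 1 hematology is every 7 days, so:

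| Hold starts | Lifted | Days missed |
|---|---|---|
| Day 8 (test day) | Day 15 | 7 |
| Day 9 | Day 15 | 6 |
| Day 9 | Day 22 | 13 |
| Day 15 | Day 22 | 7 |
| Day 16 | Day 22 | 6 |

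Seven days is thus reachable but not automatic, and Section 13.2.5 allows earlier repeat counts. A hold over 14 days ends lenalidomide under 10.3, and that subject too is replaced. The same applies if the investigator stops drug under Section 10.6 for an unlisted drug-related toxicity with 7 or more days of the cycle left.

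**Step 3: effect on the decision.** The protocol states no operating characteristics for the 6-subject rule. Its lead-in maximum reproduces as 3 dose levels × 6 = 18, with no allowance for replacements.

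Let p be the rate of DLTs as defined and q the rate of unlisted drug-related holds of 7 or more days. Both are assumptions. Acceptance at DLT rate r is

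A(r) = P(0 or 1 in 6) = (1−r)^6 + 6r(1−r)^5.

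- Replaced, as written: r = p/(1−q)
- Counted as DLT: r = p+q
- Kept in the six as non-DLT: r = p

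With p = 10%, A(0.10) = 0.5314 + 0.3543 = 0.886. At q = 5%, r = 0.10/0.95 = 0.1053 if replaced and 0.15 if counted.

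| q | Replaced | Counted | Kept as non-DLT | Replaced minus kept |
|---|---|---|---|---|
| 2% | 88.2% | 84.4% | 88.6% | −0.4 points |
| 5% | 87.5% | 77.6% | 88.6% | −1.1 points |
| 8% | 86.8% | 70.4% | 88.6% | −1.8 points |
| 10% | 86.3% | 65.5% | 88.6% | −2.3 points |

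**Step 4: what the documents say about q.** Only Section 5.2.5 bears on it. The 45-patient study lists 2 Grade 4 neutropenias and no Grade 3 cytopenia. If that list is complete, 0/45 has an exact two-sided 95% upper limit of 1 − 0.025^(1/45) = 7.9%. The schedule differed and there was no cetuximab, so this is a rough guide, not a bound.

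**The case against.** **A Grade 4 threshold for blood counts is a clinical choice.** This stands. Nothing in the protocol says Grade 3 cytopenia should be dose-limiting in itself. The point here is narrower: losing 7 or more days of lenalidomide, the protocol's own threshold, to a toxicity caused by the drug.

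**A reader might infer that Section 10.3 is circular**, barring every hold until a DLT that itself needs missed doses. The documents do not support this as the natural reading. Section 8.1.2 presupposes that doses can be missed for toxicity in Cycle 1. The heading of 10.3 separates modification from interruption, and its text names interruptions and reductions separately. The contrary evidence is that Table 6 places holds under dose modification. The non-resolution route also gives listed toxicities a way to become DLTs without missed doses. The conflict in Step 1 does not need the circular reading.

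**A reader might infer that replacement inflates acceptance.** It does not. Compared with keeping these subjects as non-DLTs, replacement lowers acceptance by 0.4 to 2.3 points under the assumptions above.

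**The events are not lost.** Replaced subjects stay in the safety population, Section 5.2.5 expects better tolerability outside hematologic disease, and doses may be modified at any time in the proof-of-concept and expansion parts. All true, and it limits the harm. It does not bring the events into the MTD rule or resolve the conflicting instructions.

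**Conclusion.** The point holds in two parts. Section 10.3 and Table 6 conflict for Grade 3 cytopenia in lead-in Cycle 1, even on the reading kindest to the protocol. And subjects who lose 7 or more lenalidomide days, or leave the study in Cycle 1, because of an unlisted drug-related toxicity are replaced and never count in the 1-of-6 rule.

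It does not hold that every Grade 3 cytopenia leads to replacement: shorter holds leave the subject evaluable.

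The size is unknown, because the documents give no hold rate. At an assumed 10% listed-DLT rate and 5% unlisted holds, acceptance is 87.5% as written and 77.6% if counted, a gap of 9.9 points; at 2% holds it is 3.7 points (88.2% against 84.4% before rounding). The gap reflects whether a drug-stopping toxicity counts. Much higher hold rates would give more striking contrasts, but nothing in the documents supports them. This should be fixed, since the remedy is wording and the result sets the dose for the later parts.

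**What to change.** (a) **Section 10.3:** state that Table 6 holds, and the reduction Table 6 requires on resuming, are allowed in lead-in Cycle 1, and that all other Cycle 1 modifications wait for a DLT. Freeing holds alone would not be enough, because the reduction after a short Grade 3 hold would still be barred.

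(b) **Section 8.1.2 and synopsis:** count as a DLT 7 or more lenalidomide days missed, or permanent lenalidomide discontinuation, in Cycle 1 due to a toxicity suspected to be related to lenalidomide that required a Table 6 hold or stop. Keep the treated cetuximab-rash exception and the present cetuximab missed-dose criterion.

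(c) **Section 8.1.2 and synopsis:** limit replacement for missed lenalidomide to reasons not suspected to be drug-related.

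**Cost:** a wording amendment, no extra visits. Item (b) also reaches long holds for toxicities such as Grade 2 arrhythmia or allergic reaction, for which Table 6 orders a hold; the sponsor should accept that knowingly. The chance of opening the 20 mg cohort rises. At p = 10% and q from 2% to 10%, it is 11.8% to 13.7% as written (1 minus the replaced column) and 15.6% to 34.5% if all such holds count. That brings some risk of choosing a lower dose than needed. The cohort is 6 subjects, within the planned 18.

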### **8.1.3. Safety Lead-In Definition of MTD**

The MTD of lenalidomide will be defined as the highest dose level at which no more than 1 out of 6 subjects experience a DLT during Cycle 1 of lenalidomide in combination with cetuximab.

Safety measurements and analysis will be performed at each visit as outlined in [Table 2](#).

**Table 5: Schedule of Lenalidomide Safety Lead-In Dosing**

| Dose Level                            | Lenalidomide Dose (PO)
Days 1-28 of a 28-Day Cycle | Cetuximab Dose (IV) Day 1, 8, 15 &
22 of each 28-Day Cycle                           |
|---------------------------------------|-------------------------------------------------------|-----------------------------------------------------------------------------------------|
| 1
Initial Dose Level | 25 mg                                                 | 400 mg/m  initial infusion only, then
250 mg/m  subsequently |
| 2                                     | 20 mg                                                 |                                                                                         |
| 3                                     | 15 mg                                                 |                                                                                         |

## 8.2. Phase 2b – Proof of Concept

Once dosing has been established in the Safety Lead-in part, POC will be established with up to approximately 82 additional subjects enrolled to receive oral lenalidomide in combination with cetuximab (at the MTD determined during the Safety Lead-in part of the study) or as a single agent. Subjects meeting all eligibility criteria will be enrolled into one of the following two treatment arms and randomized 1:1 ratio by IVRS:

- Arm 1 (up to 41 subjects): Daily oral lenalidomide (dose determined from Safety Lead-in part) on Days 1-28 plus IV infusions of cetuximab (400 mg/m^2 initial infusion only, then 250 mg/m^2 subsequently) administered on Days 1, 8, 15, and 22 of each 28-day cycle.
- Arm 2 (up to 41 subjects): Daily oral lenalidomide 25 mg on Days 1-28 of each 28-day cycle.

Study treatment will continue until documented tumor progression per RECIST 1.1, unacceptable toxicity, death, or treatment discontinuation for any other reason.

The study may proceed to Phase 2b – Expansion part if the response rate from either arm in the Phase 2b – POC part is deemed significantly higher than 10%.

Conventional (or spiral) CT/MRI imaging is required. To ensure comparability, baseline methods and on-study methods for tumor assessment must be performed using identical techniques.

Study treatment will continue until documented tumor progression per RECIST 1.1, unacceptable toxicity, death, or treatment discontinuation for any other reason.

## 8.3. Phase 2b – Expansion

Subjects meeting all eligibility criteria will be enrolled by IVRS to take oral lenalidomide (dose determined from Safety Lead-in part) on Days 1-28 plus IV infusions of cetuximab (400 mg/m^2 initial infusion, then 250 mg/m^2 subsequently) administered on Days 1, 8, 15, and 22 of each 28-day cycle. Celgene Corporation will reassess the feasibility of adding a single agent lenalidomide arm to the Phase 2b – Expansion part of the study depending on results from the Phase 2b – POC part.

Study treatment will continue until documented tumor progression, unacceptable toxicity, death, or treatment discontinuation for any other reason.

#### **8.4. Follow-Up Period**

All study subjects who discontinue from the study for any reason other than withdrawal of consent will enter the Follow-up period that includes one follow-up visit 28 days after last dose and subsequent telephone contacts every 90 days until death or 5 years post-discontinuation.

#### **8.5. Duration of Treatment**

Subjects will be screened within 28 days of study treatment initiation. Study treatment will continue until subjects experience disease progression, unacceptable toxicity or treatment discontinuation for any other reason.

## **9. STUDY POPULATION**

### **9.1. Subject Inclusion Criteria**

Subjects must meet all of the following inclusion criteria to be eligible for enrollment into the study:

#### **9.1.1. Disease Characteristics**

1. Histologically or cytologically confirmed metastatic colorectal adenocarcinoma.
2. At least one unidimensionally measurable lesion.
3. Documented KRAS mutant tumor (paraffin tumor blocks or approximately 25 unstained slides must be sent for KRAS mutation testing and results reported by central pathology laboratory prior to study enrollment).
4. Imaging confirmed (CT/MRI) disease progression within 42 days of previous treatment.
5. Disease progression on oxaliplatin- AND irinotecan-containing regimens in the metastatic setting, with at least one of these regimens containing bevacizumab.

#### **9.1.2. ECOG**

6. Eastern Cooperative Oncology Group performance status of  $\leq 1$ .

#### **9.1.3. Pregnancy**

7. Women of childbearing potential must undergo pregnancy testing based on the frequency outlined in Section 21.3 or 21.4 and pregnancy results must be negative.
8. Unless practicing complete abstinence from heterosexual intercourse, sexually active WCBP must agree to use adequate contraceptive methods as specified in Section 21.3 or 21.4.
9. Males (including those who have had a vasectomy) must use barrier contraception (condom) when engaging in sexual activity with WCBP as specified in Section 21.3 or 21.4.
10. Males must agree not to donate semen or sperm during the duration specified in Section 21.3 or 21.4.
11. All subjects must:
  - Understand that the investigational product could have a potential teratogenic risk.
  - Agree to abstain from donating blood while taking investigational product and following discontinuation of investigational product (see Section 21.3 or 21.4).
  - Agree not to share study medication with another person.
  - Be counseled about pregnancy precautions and risks of fetal exposure (see Section 21.3 or 21.4).

#### **9.1.4. General**

12. Understand and voluntarily sign an ICF.
13. Age  $\geq 18$  years at the time of signing the ICF.
14. Able to adhere to the study visit schedule and other protocol requirements.

